### Study design and population

2.1

The SMART-CARE study is a multicenter, prospective, observational cohort trial, designed to evaluate the clinical utility of artificial intelligence (AI)-enabled remote monitoring in patients with CHF. A prospective, non-randomized observational design was chosen for both ethical and pragmatic reasons. Allocation to the intervention group required patients' explicit willingness to use the wearable device and to undergo continuous monitoring, making randomization unfeasible. To minimize potential selection bias, statistical adjustment methods (multivariable regression, propensity score matching, and stratified analyses by age, sex, New York Heart Association class - NYHA, Left Ventricular Ejection Fraction - LVEF phenotype, and comorbidities) will be applied. The trial will be conducted across three tertiary care centers in Italy: AOU “San Giovanni di Dio Ruggi d'Aragona”, IRCCS Neurolesi “Bonino Pulejo”, and IRCCS Fondazione Casa Sollievo della Sofferenza. The study will enroll 300 adult patients (≥18 years) with a confirmed diagnosis of CHF, including Heart Failure with reduced Ejection Fraction (HFrEF), Heart Failure with mildly reduced Ejection Fraction (HFmrEF), or Heart Failure with preserved Ejection Fraction (HFpEF) for at least six months, who are clinically stable and on optimized medical therapy for at least one month prior to enrolment (Figure 1).

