### Groups and interventions

2.2

Participants will be allocated to one of two non-randomized, parallel groups based on their acceptance to use the wearable device:
Intervention Group – AI-Based Remote Monitoring: Patients in this group will wear wearable devices continuously over a six-month period. The wearable device collects multimodal biometric data, including SpO₂, HRV, EDA, respiratory rate, skin temperature, pulse rate, and sleep metrics (actigraphy). These data are automatically transmitted to the SMART-CARE platform, where advanced AI algorithms analyse trends and detect early signs of clinical deterioration. In case of abnormal findings, the system generates alerts for the clinical team, which may initiate teleconsultations, therapy adjustments, or in-person evaluations to prevent acute decompensation.Control Group – Standard Clinical Follow-Up: Participants in the control group will receive standard CHF management in accordance with current European Society of Cardiology (ESC) guidelines. This includes outpatient visits every three months, ECG and echocardiographic assessments, and laboratory evaluations. No remote monitoring will be applied in this group. Clinical decisions, including medication adjustments, will be based on periodic clinical evaluations and patient-reported symptoms.

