#### Primary endpoint analysis

2.6.1

To assess the primary endpoint of the study, Kaplan–Meier survival curves will be constructed to compare the time to first hospitalization between groups. Group differences will be evaluated using the log-rank test. Subsequently, a Cox proportional hazards regression analysis model will be performed to examine the association between the variable “Device Use (Yes vs. No)” and the reduction in hospital admissions. The model will be adjusted for all statistically significant covariates identified through ANOVA between the two groups. To mitigate selection bias resulting from the non-randomized design, propensity score methods will be applied. The propensity score will be estimated using baseline variables including age, sex, LVEF phenotype, NYHA class, major comorbidities (hypertension, atrial fibrillation, diabetes mellitus, COPD/OSA, obesity), prior HF hospitalizations, baseline biomarkers (BNP/NT-proBNP, renal function, electrolytes), and key echocardiographic indices (LVEF, LV volumes). A 1:1 nearest-neighbour matching approach without replacement will be used. Covariate balance between groups will be evaluated using standardized mean differences (SMD), with values <0.10 indicating adequate balance. Results will be expressed as hazard ratios (HR) with corresponding 95% confidence intervals (CI).

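### Centre is not named among the propensity score variables or stratified analyses and is not secured in the Cox model, so centre differences in device acceptance and admission practice could appear as a device effect

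*Protocol article*

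**What the plan says.** Section 2.1 of the protocol article states that "The trial will be conducted across three tertiary care centers in Italy". Section 2.2 sets the allocation rule: "Participants will be allocated to one of two non-randomized, parallel groups based on their acceptance to use the wearable device". No allocation ratio and no balancing by centre is given.

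Against the resulting selection bias, section 2.1 promises multivariable regression, propensity score matching and "stratified analyses by age, sex, New York Heart Association class - NYHA, Left Ventricular Ejection Fraction - LVEF phenotype, and comorbidities". Section 2.6.1 gives the detail. The score is introduced with "The propensity score will be estimated using baseline variables including age, sex, LVEF phenotype, NYHA class, major comorbidities" and the list continues to "prior HF hospitalizations, baseline biomarkers (BNP/NT-proBNP, renal function, electrolytes), and key echocardiographic indices (LVEF, LV volumes". Matching is 1:1 nearest neighbour without replacement, and balance is judged adequate when standardized mean differences (SMD) are below 0.10. The Cox model is adjusted for covariates that an ANOVA between the groups finds significant. Section 2.6.2 stratifies the secondary endpoints by LVEF phenotype.

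Centre or site is named as an analysis variable in none of these places, nor in section 2.6.4 on missing data. The Limitations acknowledge selection bias but not centre, and the Discussion mentions the multicentre setting only as a strength.

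**The concern.** In a cohort where patients choose their own group, a variable confounds if it is related both to that choice and to the outcome. Centre could be related to both. Acceptance may depend on how the device is offered locally. The endpoint in section 2.4 counts emergency department visits as well as unplanned hospitalizations, and both are open to local thresholds.

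Every named score variable is a patient characteristic. Two patients with the same score may therefore come from different hospitals, and nearest-neighbour matching as written can pair them. Such a pair compares the two hospitals' practice as well as device against no device. SMDs computed on the listed variables would not reveal it, because centre is not one of them. What is at stake is the reading of the primary endpoint: a centre difference could add to, or hide, a device effect.

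**Working it through.** **Step 1: where centre could enter.** The main point is settled by reading the text.

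| Place | Variables named | Centre |
|---|---|---|
| 2.1, stratified analyses | age, sex, NYHA class, LVEF phenotype, comorbidities | not named |
| 2.6.1, propensity score | the above plus prior HF hospitalizations, biomarkers, echo indices (open list) | not named |
| 2.6.1, matching | nearest score only | no restriction |
| 2.6.1, Cox model | whatever passes the ANOVA screen | possible, not secured |
| 2.6.2, secondary endpoints | LVEF phenotype | not named |

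ANOVA compares the means of a quantitative variable. Centre is a three-level label without a mean, so it is unclear that the screen would be applied to it at all.

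**Step 2: how large the effect could be.** The protocol gives neither acceptance nor risk by centre, so all inputs here are assumptions: 100 patients per centre, no true device effect, and acceptance falling as risk rises across centres. With acceptance a and six-month risk r in each centre:

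- device risk = Σ(100·a·r) / Σ(100·a)
- control risk = Σ(100·(1−a)·r) / Σ(100·(1−a))

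Each group has 150 patients in every scenario.

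| Acceptance (%) | Risk (%) | Device events | Control events | Crude risk ratio |
|---|---|---|---|---|
| 60/50/40 | 35/40/45 | 21+20+18 = 59 | 14+20+27 = 61 | 0.967 |
| 70/50/30 | 35/40/45 | 24.5+20+13.5 = 58 | 10.5+20+31.5 = 62 | 0.935 |
| 70/50/30 | 30/40/50 | 21+20+15 = 56 | 9+20+35 = 64 | 0.875 |
| 80/50/20 | 30/40/50 | 24+20+10 = 54 | 6+20+40 = 66 | 0.818 |

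The third row is 37.3% against 42.7%. If the gradients run in opposite alignment, the ratios exceed 1. If either acceptance or risk is equal across centres, the ratio is 1.00. A comparison within centre gives 1.00 in every row. The range depends on the inputs: with risks of 20/30/40%, acceptance 70/50/30% gives 41/49 = 0.84 and 80/50/20% gives 39/51 = 0.77.

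**Step 3: would the Cox screen catch it?** Suppose centre were a candidate and were tested with a chi-square test on the 3 × 2 table of centre by group, with 50 expected per cell. The two outer centres contribute two cells each:

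- 60/50/40: 4 × 10²/50 = 8 (2 df, p = 0.018)
- 70/50/30: 4 × 20²/50 = 32
- 80/50/20: 4 × 30²/50 = 72

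Centre would pass in all these scenarios. The gap is that nothing makes it a candidate, and the named test is not one for such a variable.

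**Step 4: price of exact matching on centre.** The most pairs available within a centre is the smaller of its two groups.

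- 70/50/30: 30 + 50 + 30 = 110 of 150 pairs (27% lost)
- 80/50/20: 20 + 50 + 20 = 90 of 150 pairs (40% lost), that is 180 patients, below the 186 required in section 2.6.3

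**The case against.** This is a condensed article, its score list is explicitly open, and how centre is handled is often settled in an analysis plan. A reader might infer that centre has been excluded. The text does not say so; it only fails to name it. What keeps the point alive is the level of detail. Section 2.6.1 goes down to electrolytes, ventricular volumes, the replacement rule and an SMD threshold, yet names no design-level variable.

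A reader might also infer that a spurious effect survives every adjustment in the plan. That is not shown. The Cox screen could admit centre (step 3), and any between-centre risk difference that comes from case mix would be partly removed by NYHA class, prior hospitalizations, biomarkers and LVEF. The ratios in step 2 are crude and assume that acceptance and risk line up perfectly. They do not measure what remains after adjustment.

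It is tempting to add that separate teams answer the alerts at each hospital. Section 2.2 speaks of one clinical team without describing teams by centre. Variation in alert response would in any case concern how the intervention is delivered in the device group, and would not be a source of spurious effect. Eligibility, visit schedule and guideline care for controls are common to all centres, which limits centre differences but does not remove local thresholds for emergency visits and admission.

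**Conclusion.** The point holds as a gap in what the plan secures: centre is not named in the score or the stratified analyses, and its place in the Cox model rests on a screen ill-suited to it. Bias follows only if both acceptance and admission practice differ by centre beyond the listed covariates. Whether they do, and by how much, cannot be known from the document. Crude risk ratios of 0.97 to 0.82 under the four assumed scenarios show only that the effect could be material beside a 20% target; they are neither an estimate nor a bound. Confidence is high for the omission and low for the size of any bias. This is a cheap improvement to make before outcomes are seen, and it does not show the planned analysis to be invalid.

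**What to change.** In section 2.6.1:

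- Include centre as a fixed term in the propensity score and report its balance after matching with the other variables.
- Stratify the log-rank test and the Cox model by centre, whatever the significance screen shows. Centre in the score does not force pairs from the same hospital, so the stratification deals with imbalance that remains.
- Report device acceptance and events by group and centre, so that readers can judge whether the conditions for bias were present.

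Keep exact matching within centre as an optional sensitivity analysis, because step 4 shows that it loses most pairs where acceptance differs most.

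The change is one of analysis wording, as each patient's enrolling centre is known. With three centres the score term costs two degrees of freedom, and some pairs may be lost.

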Optimized heart failure therapy for at least 1 month prior to enrolment	Terminal illness with limited life expectancy (e.g., metastatic cancer, end-stage lung disease)
Any LVEF phenotype (HFrEF, HFmrEF, HFpEF)	Pregnancy
≥1 hospitalization or outpatient visit with IV therapy for CHF in last 12 months	Dermatological conditions or allergies preventing prolonged use of the wearable device
Ability to provide informed consent or availability of a legally authorized representative	Cognitive or psychiatric disorders impairing adherence to study procedures

CHF, chronic heart failure; eGFR, estimated Glomerular Filtration Rate; HFmrEF, Heart Failure with mildly reduced Ejection Fraction; HFpEF: Heart Failure with preserved Ejection Fraction; HFrEF, Heart Failure with reduced Ejection Fraction; IV, intravenous; LVEF, left ventricular ejection fraction; NYHA, New York Heart Association; VAD, ventricular assist device.

All clinical, instrumental, and biochemical data will be recorded in anonymized case report forms and stored in a secure digital database. Biospecimens (blood and urine) will be collected and retained for secondary biomarker analysis. The study protocol adheres to the Declaration of Helsinki and Good Clinical Practice guidelines, and it was approved by the regional ethics committee (Comitato Etico Campania 2; Approval No. 185867). The trial is registered at ClinicalTrials.gov with the identifier NCT06909682.

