### Outcomes

2.4

Both groups will undergo assessments at baseline, 3 months, and 6 months, including evaluations of functional status, echocardiographic parameters, biochemical markers (e.g., BNP, NT-proBNP, renal function), and quality of life assessed using the Kansas City Cardiomyopathy Questionnaire (KCCQ) (36–39) (Table 2).

**Table 2 T2:** SMART-CARE outcome measures by timepoint.

Outcome type	Outcome measure	Domain	Baseline	3 months	6 months
Primary	Change in Hospital Admissions	Clinical Events			✔
Secondary	Change in Quality of Life (KCCQ Score)	Quality of Life	✔	✔	✔
Secondary	Adverse Effects of CHF Therapy	Safety			✔
Secondary	Change in BNP Levels	Biochemical	✔	✔	✔
Secondary	Change in NT-proBNP Levels	Biochemical	✔	✔	✔
Secondary	Change in Serum Creatinine	Biochemical	✔	✔	✔
Secondary	Change in eGFR	Biochemical	✔	✔	✔
Secondary	Change in Serum Sodium	Biochemical	✔	✔	✔
Secondary	Change in Serum Potassium	Biochemical	✔	✔	✔
Secondary	Change in Serum Chloride	Biochemical	✔	✔	✔
Secondary	Change in HRV	Functional (ECG)	✔	✔	✔
Secondary	Change in Respiratory Rate	Functional (ECG)	✔	✔	✔
Secondary	Change in LVEF	Echocardiographic	✔	✔	✔
Secondary	Change in E/A Ratio	Echocardiographic	✔	✔	✔
Secondary	Change in LV End-Diastolic Volume	Echocardiographic	✔	✔	✔
Secondary	Change in LV End-Systolic Volume	Echocardiographic	✔	✔	✔

CHF, chronic heart failure; KCCQ, Kansas City Cardiomyopathy Questionnaire; BNP, B-type Natriuretic Peptide; NT-proBNP, N-terminal pro-B-type Natriuretic Peptide; eGFR, estimated Glomerular Filtration Rate; HRV, Heart Rate Variability; ECG, Electrocardiogram; LVEF, Left Ventricular Ejection Fraction; E/A Ratio, Early to Late Ventricular Filling Velocity Ratio; LV, left ventricle.

The primary outcome of the SMART-CARE study is the relative reduction (≥20%) in hospital admissions, including emergency department visits and unplanned hospitalizations, over a six-month follow-up period in the intervention group compared to standard care (40). Hospitalization data will be collected prospectively and analysed for frequency, duration, and cause.

Secondary outcomes include:

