Quality of Life (QoL): Measured using KCCQ at baseline, 3 months, and 6 months.Biochemical parameters: BNP, NT-proBNP, serum creatinine, eGFR, and serum electrolyte levels (sodium, potassium, chloride) at 3 and 6 months.Functional parameters: Variations in HRV and RR derived from wearable sensor data.Echocardiographic measures: LVEF, Early to Late Ventricular Filling Velocity Ratio (E/A ratio), and left ventricular end-diastolic and end-systolic volumes, measured at 3 and 6 months.Adverse events: Incidence of therapy-related complications such as hypotension and bradyarrhythmias.These outcomes will provide a comprehensive evaluation of the impact of AI-driven remote monitoring clinical status, functional performance, biomarker trends, and patient-reported outcomes in individuals with CHF. The measurements collected by the minimally invasive devices will be uploaded to the “Smartcare” platform and analyzed using machine learning (ML) techniques to develop multiparametric scores capable of identifying the specific trajectory of patients affected by HF.

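### Baseline KCCQ is measured in both self-selected groups but is not named in the propensity score, and its only other route into the primary analysis is a significance screen that misses moderate imbalance

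*Protocol article*

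**What the plan says.** Section 2.2 describes how the groups form: "Participants will be allocated to one of two non-randomized, parallel groups based on their acceptance to use the wearable device". Section 5 lists selection bias as the first limitation and relies on statistical adjustment to reduce it.

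That adjustment is set out in Section 2.6.1. "The propensity score will be estimated using baseline variables including age, sex, LVEF phenotype, NYHA class, major comorbidities" is followed by a bracketed list of comorbidities and then by "prior HF hospitalizations, baseline biomarkers (BNP/NT-proBNP, renal function, electrolytes), and key echocardiographic indices (LVEF, LV volumes". Matching is one to one, and an SMD below 0.10 counts as adequate balance. Separately, the Cox model takes in those covariates that an ANOVA between the two groups finds significant. Section 2.1 adds stratified analyses by age, sex, NYHA class, LVEF phenotype and comorbidities.

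Section 2.4 states "Both groups will undergo assessments at baseline, 3 months, and 6 months", and quality of life is "Measured using KCCQ at baseline, 3 months, and 6 months". Table 2 ticks the baseline column for "Change in Quality of Life (KCCQ Score". KCCQ appears in neither the propensity-score list nor the stratification factors.

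Table 1 requires "≥1 hospitalization or outpatient visit with IV therapy for CHF in last 12 months". Of that history, the propensity score names only prior HF hospitalizations.

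**The concern.** Willingness to wear a device for six months may well depend on how ill the patient feels, and so may the chance of an emergency visit or unplanned admission, which make up the primary outcome. A baseline variable that acts on both confounds the device comparison unless it is adjusted for.

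KCCQ is the trial's only patient-reported health-status measure, and it is already collected before follow-up. NYHA class is in the score, but only three classes are eligible (I to III), so it is a coarse substitute. What is at stake is the primary hazard ratio: a residual difference in health status could in part be credited to the device, or could hide a device benefit.

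**Working it through.** No figure in the plan is being reproduced here. The check compares the covariate list with the data collected, then asks what the remaining adjustment route would catch.

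**Step 1. List against data collected.**

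| Baseline item | Collected in both groups? | Named in the propensity score? |
|---|---|---|
| NYHA class, BNP/NT-proBNP, renal function, electrolytes, LVEF, LV volumes | Yes | Yes |
| KCCQ | Yes (Section 2.4, Table 2) | No |
| Prior HF hospitalizations | Implied by the list | Yes, form not specified |
| Time since the qualifying HF event | Not stated | No |
| Outpatient IV-therapy visit as the qualifying event | Not stated | No, partly implied by hospitalization history |

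**Step 2. What the ANOVA screen can detect.** Inputs: two-sided 0.05 (Section 2.6.2); 300 patients (Section 2.6.3); 150 per group is an assumption, because the split is not stated. For two groups the smallest observed SMD that reaches significance is 1.96 × √(1/n₁ + 1/n₂).

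- 150 and 150: 1.96 × √(2/150) = 1.96 × 0.1155 = 0.23.
- 200 and 100, as a less even split: 1.96 × √(1/200 + 1/100) = 1.96 × 0.1225 = 0.24.
- 100 matched pairs, if the screen were run after matching: 1.96 × √(2/100) = 0.28.

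An observed KCCQ imbalance between 0.10 and about 0.23 therefore exceeds the plan's balance limit without triggering adjustment.

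**Step 3. Size of the distortion.** Assume a true hazard ratio of 1, better KCCQ among acceptors, and a hazard ratio g per SD of *worse* KCCQ. All values of g are assumptions. The apparent hazard ratio is g^(−SMD).

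| g per SD | SMD 0.10 | SMD 0.23 |
|---|---|---|
| 1.2 | 0.98 | 0.96 |
| 1.3 | 0.97 | 0.94 |
| 1.5 | 0.96 | 0.91 |

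If sicker patients accept more often, the sign flips: at SMD 0.23 the apparent ratio is 1/0.96 = 1.04 to 1/0.91 = 1.10.

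These figures assume that KCCQ is uncorrelated with the listed covariates. Correlation with NYHA class, natriuretic peptides or prior HF hospitalizations would shrink them.

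**The case against.** The strongest objection is that the list opens with the word *including*. In a condensed article, a variable's absence from such a list does not prove its exclusion from the model, and the full list may sit in a document not shown. That stands as far as it goes: the text permits KCCQ. But it does not commit to it, although it itemises down to electrolytes and LV volumes. The only rule stated for other variables is the significance screen.

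Second, that screen is a real safeguard. An imbalance of 0.30 SD would give z = 0.30/0.1155 = 2.6, p about 0.01, and KCCQ would enter the Cox model. This is correct and limits the gap to roughly 0.10 to 0.23.

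Third, the score already carries symptom class, biomarkers, comorbidities and hospitalization history. These are partial proxies, so the Step 3 figures are before shrinkage.

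Several stronger readings are tempting but not supported:

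- A reader might infer that the date and type of the qualifying event are recorded for every patient and then ignored. Eligibility requires such an event, but nothing says either detail is kept as a variable. Hospitalization history also covers event type in part, since a patient with none in the 12-month window must have qualified by an IV-therapy visit.
- A reader might infer that patients can enter the day after a decompensation. Section 2.1 asks for clinical stability and a month of optimized treatment, which at least makes that unclear.
- A reader might infer that the bias must favour the device. Recently unwell patients could be keener to be monitored, and the protocol supports neither direction.
- A reader might multiply a KCCQ effect by a recency effect and reach a spurious reduction of 10 to 17%, close to the 20% target. That requires assumed effects that probably overlap, a recency term not reduced for the listed covariates, and at the upper end a KCCQ imbalance that the ANOVA screen would normally catch.

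**Conclusion.** The point holds for KCCQ. Allocation is by self-selection, the measure is available at baseline in both groups, and it is not named in the score. The fallback route misses imbalances that the plan's own criterion would call inadequate. The resulting bias in the primary hazard ratio is of modest size: at the top of the gap, an apparent 0.96 to 0.91 (or 1.04 to 1.10 in the other direction), before shrinkage. This rests on 150 patients per group and a hazard ratio of 1.2 to 1.5 per SD, neither of which the protocol gives. It would not by itself produce a 20% reduction, but several percent matters against a 20% target. For time since, and type of, the qualifying event, the point is conditional on those details being recorded.

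**What to change.** In Section 2.6.1, name the baseline KCCQ score, as a continuous variable, in the propensity score and in the adjusted Cox model, regardless of its between-group p-value. Report its SMD with the others.

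Where the eligibility check leaves a record of the qualifying HF event, add time since that event and its type (hospitalization or outpatient IV therapy) in the same way.

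The cost is a sentence or two in the analysis section and one to four more parameters in the score. KCCQ needs no new data collection.

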## Limitations

5

This study has several potential limitations that should be acknowledged. First, the non-randomized design may introduce selection bias, although the use of statistical adjustment methods (including multivariable regression and propensity score analyses) is expected to mitigate this risk. Second, the adoption of wearable devices may be influenced by a digital divide, with older or less digitally literate patients potentially underrepresented in the intervention group, which could limit the generalizability of the findings. Third, the reliance on continuous biometric monitoring and AI-driven alert generation raises the possibility of false positives, which may result in unnecessary clinical evaluations and potentially increase healthcare utilization. Conversely, false negatives cannot be excluded, with the risk of delayed detection of clinical deterioration. Finally, adherence to wearable use may vary over time, and incomplete data capture could affect the robustness of the analyses.

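### Choosing Cox covariates by between-group significance lets through imbalances that the plan's own SMD limit calls inadequate; a prespecified adjustment set, with ICD/CRT status added, is a cheap improvement (low to moderate priority)

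*Protocol article*

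**What the plan says.** All references are to the protocol article.

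- **Allocation.** Section 2.1 says that joining the intervention group depends on the patient's "explicit willingness to use the wearable device and to undergo continuous monitoring, making randomization unfeasible". Section 2.2 confirms that the groups form by acceptance of the device.
- **Reliance on adjustment.** Section 5 (Limitations) acknowledges selection bias and says that "the use of statistical adjustment methods (including multivariable regression and propensity score analyses) is expected to mitigate this risk".
- **Propensity score, Section 2.6.1.** "The propensity score will be estimated using baseline variables including age, sex, LVEF phenotype, NYHA class, major comorbidities", followed by named comorbidities and then "prior HF hospitalizations, baseline biomarkers (BNP/NT-proBNP, renal function, electrolytes), and key echocardiographic indices (LVEF, LV volumes". Matching is one-to-one by nearest neighbour.
- **Balance standard, Section 2.6.1.** "Covariate balance between groups will be evaluated using standardized mean differences (SMD), with values <0.10 indicating adequate balance".
- **Cox covariates, Section 2.6.1.** "The model will be adjusted for all statistically significant covariates identified through ANOVA between the two groups". The section gives no other selection rule, and it does not say whether the Cox model is fitted in the matched set or in the full cohort.
- **Implanted devices.** The Introduction says that implantable defibrillators, with or without resynchronisation therapy, carry algorithms that watch for congestion. Table 1 admits "Any LVEF phenotype (HFrEF, HFmrEF, HFpEF") and has no exclusion for implants, so carriers are eligible. Implant status is not named in the propensity list or among the stratification factors in Section 2.1.

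**The concern.** In a self-selected comparison, a covariate confounds according to how far it differs between groups and how strongly it predicts the outcome. A between-group p-value measures neither well. It mixes the size of the imbalance with the sample size and ignores prognosis. Section 2.6.1 accepts the point in its balance check, where it uses the SMD, but then uses significance to decide what the Cox model adjusts for.

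The two rules disagree over a range of imbalances. A covariate can fail the plan's definition of adequate balance and still be left out of the model that yields the primary hazard ratio. For variables in the propensity score, matching is a second line of defence. For any variable outside it, the significance screen is the only stated safeguard.

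ICD/CRT status shows the gap. Patients select themselves on willingness to be monitored, the protocol itself links these implants to congestion monitoring, carriers may enrol, and the variable is not named in the score. At stake is some residual confounding in the primary comparison.

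**Working it through.** There is no computed figure in the plan to reproduce on this point. The SMD limit of 0.10 is a chosen threshold, and the sample-size figure in Section 2.6.3 does not enter.

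**Inputs from the protocol.** Planned enrolment 300 (Section 2.6.3); two-sided p < 0.05 for significance (Section 2.6.2, taken here to apply to the screen); SMD limit 0.10 (Section 2.6.1).

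**Assumed inputs.** Group sizes and numbers of matched pairs, which are not stated. In the illustrations, also the carrier shares, the carriers' risk ratio and the fraction of imbalance that matching removes.

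**Step 1: the SMD at which the screen triggers.** With two groups, one-way ANOVA is the two-sample t-test, so the smallest observed SMD that reaches p = 0.05 is

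SMD = t(0.975, n1+n2−2) × √(1/n1 + 1/n2)

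| Groups | Cut-off SMD |
|---|---|
| 150 / 150 | 0.227 |
| 100 / 200 (either way) | 0.241 |
| 75 / 225 | 0.262 |
| 60 / 240 | 0.284 |
| 100 matched pairs | 0.279 |
| 75 matched pairs | 0.323 |

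Every cut-off is more than twice the plan's 0.10. At 150/150, observed SMDs of 0.10, 0.15 and 0.20 give p = 0.39, 0.20 and 0.08, so none is selected. For an SMD of 0.10 to reach p = 0.05 would take 2 × (1.96/0.10)² ≈ 768 patients per group.

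**Step 2: how often the screen catches a true imbalance.** By the noncentral t distribution at 150/150, true SMDs of 0.10, 0.15 and 0.20 are selected 14%, 25% and 41% of the time.

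**Step 3: a binary covariate such as ICD/CRT.** SMD = |p1−p2| / √[(p1(1−p1)+p2(1−p2))/2].

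- Observed 24/150 v 37/150 (16.0% v 24.7%): SMD 0.217, chi-square p = 0.062. It is more than double the limit and is not adjusted for.
- True shares 15% v 25% (SMD 0.252): flagged 59% of the time at 150/150, and 55% or 52% at 200/100 or 100/200 (exact enumeration of two binomials).
- True shares 20% v 25% (SMD 0.120): flagged 18% of the time at 150/150.

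**Step 4: what might remain for ICD/CRT (illustration only).** The spurious ratio is (1 + p1(RR−1)) / (1 + p2(RR−1)), starting from a crude 15% v 25%. RR is the risk ratio for carriers that remains after the listed covariates.

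| Difference removed by matching | RR 1.2 | RR 1.5 | RR 2.0 |
|---|---|---|---|
| Half (17.5% v 22.5%) | 0.990 | 0.978 | 0.959 |
| Three quarters (18.75% v 21.25%) | 0.995 | 0.989 | 0.979 |

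That is a spurious change of 0.5% to 4.1%, and its direction reverses if the shares reverse. For scale, the standard error of the log hazard ratio is at least 2/√300 = 0.115, even if all 300 patients had an event in equal groups. The largest case, |ln 0.959| = 0.042, is 0.042/0.115 = 0.36 of that floor. Fewer events would make the fraction smaller.

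**The case against.** The strongest reply has four parts.

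- **The two rules have different jobs.** The SMD governs matching and significance governs the Cox model. A listed covariate is matched and checked at 0.10 whatever the ANOVA shows. This stands in part: Steps 1 to 3 describe the Cox screen, not the whole adjustment plan. It does not cover variables outside the score. Nor does it cover the listed ones if the Cox model is fitted in the full cohort, which Section 2.6.1 leaves open.
- **The propensity list is open.** It is introduced by the word including, the article is condensed, and Section 2.1 says that "All clinical, instrumental, and biochemical data will be recorded in anonymized case report forms and stored in a secure digital database". This stands. ICD/CRT status may already be captured and may be in the full list, so its absence from the article is not in itself an error. The significance rule is different, because it is stated outright.
- **Nothing links implants to acceptance of the wearable.** This stands. The link is an inference from the Introduction and from how the groups form. LVEF, NYHA class, prior admissions, natriuretic peptides and ventricular volumes also partly stand in for implant status.
- **The residual bias is small and rests on assumed inputs.** This stands too.

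A reader might go further and infer that implant carriers in the control group are in effect remotely monitored, or that the primary comparison is shown to be biased. The documents support neither. The Introduction says only that the implants monitor signs of congestion, not that they transmit data in this cohort. Section 2.2 says controls receive no remote monitoring, and no carrier share or outcome association is given.

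**Conclusion.** The criticism of the significance rule holds. The rule is stated, and it admits to the Cox model only imbalances of about 0.23 or more at an assumed 150/150 split (0.24 at 2:1; about 0.28 or 0.32 with 100 or 75 matched pairs), while the same section calls 0.10 or more inadequate. The size of that gap depends only on group sizes and the 5% level.

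How much bias follows is not known. For ICD/CRT it is probably small, of unknown sign, and rests wholly on assumed shares, risk ratios and matching performance. The case for naming that variable is that it is eligible, plausible and cheap, not that its omission is a demonstrated fault. Overall this is an improvement of low to moderate priority.

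**What to change.** 1. In Section 2.6.1, replace the significance rule with a Cox adjustment set fixed in advance and used whatever the between-group p-values. The preferred set is the listed propensity covariates. The minimum is every covariate with an SMD of 0.10 or more after matching, which at least brings the model into line with the plan's own limit.
2. Name baseline ICD/CRT status as one further covariate in the propensity score, the SMD table and the Cox model. Record it at baseline if the case report form does not already hold it.

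The cost is a few more model terms, at most one extra baseline item, and possibly some lost matched pairs because there is one more variable to balance. If first events prove few, the shorter set is the safer choice. Enrolment, endpoint and analysis population do not change.
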